## Abstract

Breast cancer is the most common cancer spread among women worldwide. Whereas many studies have discussed the significance of breast cancer screening among women in various countries, few have attempted to discuss this topic among female school teachers. As teachers educate and communicate with students, this may play an essential role in health education and in promoting healthy behavior, such as breast cancer screening. The primary goal of this study is to develop and implement an educational intervention of breast cancer screening and evaluate its effectiveness among Yemeni female school teachers in Malaysia. This was carried out as per the health belief model. A cluster-randomized controlled trial was conducted among 183 Yemeni female school teachers in twelve schools in Klang Valley, Malaysia. A random assignment of the target schools was made to include them within the intervention or control group. Participants in the intervention group were offered a 90-min session for one-day educational intervention on breast cancer screening. On the other hand, participants in the control group were offered the same educational materials at the end of the study. Relevant data was collected at baseline, one month following the intervention, and then three- and six-months follow-up assessments. Analysis of such data was done via IBM SPSS software 25.0 by generalized estimating equations (GEE) to assess the differential changes over time. A primary outcome embodied in breast cancer screening practice uptake was expected. Secondary outcomes include the target group’s knowledge on and beliefs of breast cancer screening. This study intends to contribute to the credibility and effectiveness of utilizing a theory-based breast cancer screening intervention in order to raise the awareness of women on conducting breast cancer screening.

## 1. Introduction

Although efforts and extensive progress have been made in medical treatment, breast cancer (BC) continues to be among the highest life-threatening diseases among women [1]. It is argued that BC mortality rates in many countries with low and middle income are higher than those in high-income countries. This could be attributed to the early diagnosis of BC in the latter countries. Unfortunately, the diagnosis of BC in the former countries is made at later stages [2]. Yemen, as one of the low-income countries, is a case in point. Most BC cases are identified at late stages or after the occurrence of metastasis [3]. Due to the recent instability of Yemen and lack of security, many Yemenis decided to immigrate to Malaysia for educational purposes and/or job opportunities or to reside as immigrants. As a result, Yemenis in Malaysia have reached a population of about 27,000 according to 2018 estimates of the Yemeni Embassy. Among these are Yemeni females who may not have any idea of BCS services and lack the knowledge and good health beliefs in this regard.

Practically speaking, BC early detection examinations help save thousands of lives each year and improve the chances for early detection of BC, and therefore successful treatment [4]. Several approaches have been evaluated in this respect, such as BCS methods, including BSE, clinical breast exam (CBE), and mammography [5]. A number of epidemiological studies have been conducted on community samples of various women groups. Such studies have shown that the rate of BCS practice was low in various countries [6,7,8]. In Yemen, the findings of similar studies on BSE show that the rate of women performing BSE ranges from 11% to 17.4% [9,10]. 

Theoretically, different models and theories have been used in order to comprehend BC early detection. One is the health belief model (HBM) that is used as the theoretical framework in numerous educational interventions. HBM has proven to be effective in improving factors impacting BCS behaviors [7,11,12,13,14]. The theoretical framework of the HBM emphasizes that threats pertaining to health concerns can negatively affect the health behavior of women. For instance, women with the feeling of being susceptible to BC risk are more likely to do BSE. Women, having good health motivation, gaining higher benefits and having fewer barriers to a breast exam are more probable to do BSE [15]. Moreover, knowledge about BCS practice is associated with an increase in performing BCS behaviors, as suggested by the model [16]. 

Many studies on BCS performance have been implemented among women worldwide. Such studies have incorporated certain women groups such as female university students, female workers, women attending health care centers, or female residents [12,17,18,19,20]. Nevertheless, only a few studies have been conducted on female teachers regarding BCS practice in the world [11,21,22,23,24,25]. For example, in Malaysia, even though a few studies have shed light on BCS practice among teachers, no research has been done on BCS practice among Yemeni female school teachers in Malaysia. As teachers, they are regarded as role models and an essential educational source. They could possibly play a vital role in offering health education and in promoting healthy behavior pertaining to BCS practice to be adopted by future generations. In addition, one day, these teachers will return to their home country and, thus, spread the knowledge they have gained in this domain. Therefore, developing and implementing this BC educational program among Yemeni female school teachers could be one of the effective means to reduce BC mortality rates within this group and develop educational programs for other groups.

In brief, interventions focusing on BC early detection are less common among school teachers, in general, and absent among Yemeni school teachers in Malaysia, in particular. Therefore, not only does the current study intend to develop and evaluate an educational intervention based on the HBM but also to educate Yemeni female school teachers in Arabic schools in Malaysia and provide them with knowledge and enhance their beliefs of BC and BCS practice. It also aims to promote BCS among them.

The overall objective of this study is to develop and evaluate the effectiveness of an educational intervention grounded in the HBM on BCS uptake (BSE, CBE, and mammography), knowledge, and beliefs among Yemeni female school teachers in Klang Valley, Malaysia. It is hypothesized that starting from baseline until the three- and six-month assessment, women in the experimental group will gain the following: i.An increase in the proportion of their BCS uptakeii.An increase in their BC knowledge scoresiii.An improvement in their BC health beliefs (perceived susceptibility, perceived seriousness, perceived benefits, perceived barriers, health motivation, confidence).

## 2. Materials and Methods

### 2.1. Study Design

This is a parallel cluster-randomized controlled trial (cRCT), with schools being the unit of randomization (clusters). The trial will be used to assess the effectiveness of an educational intervention on BCS uptake, knowledge, and beliefs of Yemeni female school teachers at both elementary and high Arabic schools in Klang Valley, Malaysia. There are nineteen well-known Arabic schools in Klang Valley area, with teachers from different Arab countries (i.e., Yemen, Iraq, Egypt, Libya, Saudi Arabia). However, the main composition of the teaching bodies is Yemeni teachers, as six of the schools are Yemeni schools. Twelve of the schools were selected as clusters (schools), and randomly assigned for the intervention or the control group. While the intervention group was given an educational intervention on BCS, the control group received the educational materials on BCS intervention after the completion of the study. 

### 2.2. Eligibility Criteria

The inclusion criteria for schools will take into account the following requirements: (1) such samples are elementary and high Arabic schools; (2) they are situated in Klang Valley; (3); and they consent to participate in the study. The exclusion criteria will disqualify Arabic schools that do not have Yemeni female teachers from the study,

The inclusion criteria for teachers takes into consideration the following requirements: (1) such participants must only be Yemeni female school teachers teaching at the selected elementary and high Arabic schools situated in Klang Valley; (2) participants are aged 20 years old or older; (3) they sign a consent form to take part in the study. The exclusion criteria for teachers include (1) teachers who are retiring during the study, (2) teachers who have been diagnosed with BC, and (3) teachers who are lactating or pregnant.

### 2.3. Intervention 

The intervention group will be introduced to an educational intervention on BCS. This intervention is grounded in the HBM and developed based on the American Cancer Society [4], American Congress of Obstetricians and Gynecologists [26], and the International Agency for Research on Cancer (IARC) [27]. Many educational interventions, being grounded in the HBM, have shown improvement in the practice of BCS behaviors on the part of relevant participants. The educational intervention module uses six constructs of the HBM: perceived susceptibility, perceived seriousness, perceived benefits, perceived barriers, health motivation, confidence. This intervention was prepared and designed to bridge the gap of BC knowledge and to modify beliefs related to BC. Table 1 gives an outline of the educational intervention on BCS along with the application of the HBM concepts in the educational intervention. 

The educational intervention consists of four units. Unit One provides general information on the anatomy and physiology of a normal breast in order for the participants to have a clear understanding of the topic. Unit Two gives information and knowledge of BC. It further explores BC symptoms, BC stages, BC risk factors in order to increase the participants’ knowledge of BC. Unit Three offers an explanation of two different methods of BCS (CBE and mammography) in a bid to encourage participants to adopt and practice these approaches. Unit Four explains the BSE procedure to raise the participants’ awareness of BC symptoms and motivate them to follow this procedure. 

Following the development of the educational intervention, face and content validity were checked and assessed by five professional expert panelists from the Community Health Department and Cancer Resource and Education Centre at the Faculty of Medicine and Health Sciences, Universiti Putra Malaysia. The experts approved the educational material as efficient with respect to the study objectives. Their feedback focused on the understandability and simplicity of the content. They suggested that information about the incidence of BC and any medical terms from the module ought to be removed because it is irrelevant to the layperson, a glossary of terms for the module ought to be drafted, and colorful pictures for the module should be included in order for the module to be clearer and more interesting. 

The educational intervention involves a 90-min session for one-day. The study researcher with the help of a trained research assistant, will conduct the session for the intervention group at each respective school. It is expected that three sessions will be carried out each week. Although the implementation date of the intervention may differ from one school to another, its duration time will be the same for all. The following is a breakdown of the procedures to be conducted:(a)A 60-min PowerPoint presentation will be delivered along with a revised five-minute short video about BSE performance provided by the permission of Nuffield Health [28]. Another five-minute short video will be shown, highlighting the testimony made by one of the BC survivors. In other words, the BC survivor will share her experience with BC and give some advice on the importance of BCS and early detection.(b)A thirty-minute training session on BSE practice on a silicone breast model with several implanted lumps will be carried out. In this session, participants will acquire knowledge on palpation technique and search strategy as well as signs of BC in order to be aware of when examining the breast. Following that, participants will be asked to perform BSE based on what they have learnt.(c)At the end of the educational intervention, participants will be offered a copy of the relevant booklet containing all the information delivered to them in the educational intervention; they will be given CDs of the five-minute short video about BSE performance, and a BC logo sticker to be hung on the participants’ mirrors. The significance of distributing such materials lies in reminding the participants of the high importance of BCS practice. Along with encouraging the performance of BSE on a monthly basis, this aims at enhancing the intended messages.(d)All participants in the intervention group will continue to receive short reminder text messages for a period of 6 months. The text message will read as: “This is a gentle reminder of BSE monthly performance and BCS practice.” The key messages will provide recommendations about BCS behaviors to remind, motivate, and encourage participants to practice BCS behaviors.

Furthermore, participants in the control group will not receive any education during the study period. However, they will be given the same educational materials on BCS at the end of the study, and they also will answer the same sets of the questionnaires at baseline, one month following the intervention, then after three- and six-months have gone by after the intervention. 

#### Intervention Fidelity

To support the fidelity of the educational intervention, some strategies are used. These include the strategy for preserving the consistency of the intervention delivery and for encouraging participants’ adherence to the intervention and reinforcing such abidance on their part. To maintain consistency in the intervention delivery, the educational intervention is implemented independently in each study cluster by the same researcher. The researcher will be committed to adopt a single educational intervention protocol to ensure a standard delivery across the respective schools. 

BSE training will be planned and rehearsed by the researcher by using a role-play technique with the participants. The researcher acts as an observer during the sessions and will provide immediate feedback to the participants. Other possible means enhancing intervention fidelity include the monthly short reminder text messages and the use of the BC logo sticker. These are mainly employed to encourage participants, remind them of the importance of BCS practice and monthly BSE performance, and to reinforce the intended messages.

### 2.4. Participant Privacy

To ensure sincere responses, honesty will be emphasized to the participants. They will be informed that all questionnaires will be anonymous with a unique number to identify participants later on. 

### 2.5. Outcome Measures

#### 2.5.1. Primary Outcomes

The primary outcome variables in the present study include

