##### The Proportion of Participants Who Perform BSE Regularly and Proficiently

BSE practice and performance frequency will be measured using a self-report answer instrument. Developed by Akhtari-Zavare et al. [12], this instrument incorporates the following questions: (a) Have you ever performed BSE [yes/no], (b) How often do you perform BSE (once a month, once in 2–3 months, other, never). 

A woman who does BSE once a month will be classified as practicing (regular BSE); any other answer will be classified as non-practicing (irregular BSE). The proficiency of performing BSE will be measured by asking the participant to perform BSE on a breast model through BSE proficiency rating instrument (BSEPRI) [29]. This instrument is a checklist assessing the participants’ skills of BSE performance. This assessment is done while the participants demonstrate BSE procedures on a breast model. Needless to say, higher scores indicate greater BSE performance.

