##### The Proportion of Participants Who Attend a Clinic for Screening CBE and Mammography

Screening practice regarding CBE and mammography will be assessed using self-report questions assessing participants as “practicing” or “not practicing”.

Using self-reporting in some of the primary outcomes may lead to some sort of bias judgment. Although unavoidable, the researcher tries to reduce this prejudice by being more objective at the data collection stage. This is by using simply precise language, maintaining a short time frame, and assuring confidentiality and anonymity of participants.

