### 2.13. Statistical Analyses

IBM SPSS Software 25.0 (SPSS Inc. Chicago, IL, USA) will be used to analyze collected data. However, missing data will be managed by adopting the intention-to-treat analysis concept. Prior to analysis, continuous variables will be checked for normality. The alpha level of significance will be set at the value of <0.05. Descriptive analysis will be employed to describe the data at baseline. Regarding the between-group comparisons, the chi-square test will be applied to compare the frequency difference of categorical data of the intervention with that of the control groups. The independent-samples *t*-test will be applied to compare the mean difference of continuous data of the intervention with that of the control group. 

Furthermore, to evaluate the changes within both groups, Cochran’s Q test will be applied to test the frequency differences of categorical data within the study groups’ overtimes. The one-way repeated measures ANOVA will be applied to identify the mean difference within the study groups for continuous variables overtimes. Generalized estimating equations will be used to test the main effect and interaction between and within the overtimes of the intervention and control groups.

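### Three to four primary measures at three follow-ups share one unadjusted 0.05, while the trial is sized for a single unnamed pair of proportions

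*Protocol article*

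**What the plan says.** All places are in the protocol article.

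- **Outcomes.** Section 2.5.1 uses the plural: "The primary outcome variables in the present study include". Its first heading is "The Proportion of Participants Who Perform BSE Regularly and Proficiently" and its second is "The Proportion of Participants Who Attend a Clinic for Screening CBE and Mammography". The text does not say whether CBE and mammography are counted jointly or separately.
- **Rules under the BSE heading.** Frequency is self-reported. Once a month counts as regular and every other answer as irregular. Proficiency comes from an observed checklist on a breast model (BSEPRI), for which "higher scores indicate greater BSE performance". No cut-off is printed, and no rule for combining the score with frequency.
- **Times.** Section 2.3 sets assessments at "baseline, one month following the intervention, then after three- and six-months have gone by after the intervention". The hypothesis in the Introduction refers to three and six months without choosing between them.
- **Tests.** Section 2.13 states: "The alpha level of significance will be set at the value of <0.05". It gives chi-square tests for between-group comparison of categorical data, without saying at which visits. It gives generalized estimating equations (GEE) for main effect and interaction, and names neither as the primary test.
- **Sizing.** Section 2.7 uses P1 = 0.71 and P2 = 0.43, two-sided alpha 0.05 and power 0.80. It does not say which outcome these proportions describe.
- **Abstract.** It speaks of one outcome: "A primary outcome embodied in breast cancer screening practice uptake was expected".

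**The concern.** The sample size treats the trial as asking one question at 5%. The outcome section asks three or four, and the analysis section gives a single general 0.05 without saying which measure, visit or GEE term answers the primary question. If each measure is tested at that level, the chance of at least one significant primary result when the programme has no effect is well above 5%.

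The BSE heading adds a choice of definition. A proportion needs a yes/no rule for each participant, and only half of this one has a printed rule. The result could be reported as regular BSE, as regular and proficient BSE, or as a proficiency score. Left open, these choices could be settled after the results are known.

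**Working it through.** **1. The plan's own sample size.** Inputs from section 2.7: P1 = 0.71, P2 = 0.43, difference 0.28, mean 0.57, design effect 1.4, allowances of 20% and 10%.

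- Printed formula: (1.96 × √(1.14 × 0.43) + 0.84 × √(0.21 + 0.25))² / 0.28² = 48.1 per arm. The standard two-proportion formula gives 48. The article states 47, which is close enough.
- Reading both allowances as losses: 47 × 1.4 / 0.8 / 0.9 × 2 = 182.8, that is 183, as stated.

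The total therefore reproduces, and it covers one comparison at two-sided 0.05.

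**2. Counting the primary measures.** Keeping the BSE heading whole and taking CBE and mammography separately gives three. Splitting BSE into regularity and proficiency gives four.

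**3. Error at one time point, independent tests.** Chance of at least one false positive = 1 − 0.95^k.

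| Tests k | Chance |
|---|---|
| 1 | 5.0% |
| 2 | 9.75% |
| 3 | 14.3% |
| 4 | 18.5% |

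**4. Correlated tests.** The article gives no correlations, so a range is assumed. Simulating four two-sided z-tests (400,000 draws, equal correlation) gives 17.4% at 0.3, 15.5% at 0.5 and 13.0% at 0.7.

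**5. If every measure were also tested at every visit.** This is a scenario only. Four measures × three visits = 12 tests.

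- Independent: 1 − 0.95^12 = 46.0%.
- Correlation 0.3 between outcomes and 0.5 between visits: 39.4%.
- Correlation 0.7 between outcomes and 0.8 between visits: 24.0%.

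(The correlation between tests of different outcomes at different visits was taken as the product of the two.)

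**6. What a correction costs at 183 participants.** Effective number per arm = 183 × 0.8 × 0.9 / 2 / 1.4 = 47.06.

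Power = Φ[(0.28 − z × √(2 × 0.57 × 0.43 / 47.06)) / √((0.71 × 0.29 + 0.43 × 0.57) / 47.06)]

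- alpha 0.05 (z = 1.960): Φ[(0.28 − 0.200) / 0.0979] = 79%.
- alpha 0.05 / 4 = 0.0125 (z = 2.498): Φ[(0.28 − 0.255) / 0.0979] = 60%.

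Keeping 80% power at 0.0125 would need 69 per arm before inflation, so 69 × 1.4 / 0.8 / 0.9 × 2 = 268.3, or 269 in total.

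**7. Title against rule for BSE.** The heading asks for a proportion meeting two conditions. Regularity has a binary rule. Proficiency has a score and a direction. Both components are collected, but the printed text does not turn them into one yes/no variable.

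**The case against.** The strongest defence is that an article condenses a fuller protocol, and that a multiplicity procedure, a scoring rule or a choice of primary contrast may stand in a document not shown. That is fair, and the absence of an adjustment method alone would not be a finding. What remains is what the article itself fixes: plural primary outcomes, one 0.05, and sizing for one comparison that it does not identify.

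Four stronger readings are tempting, and the text does not support them.

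- **Four outcomes as a minimum.** Four requires splitting the BSE heading. Kept whole, there are three measures. Two are possible if CBE and mammography are counted jointly, and two independent tests still give 9.75%.
- **Twelve tests and 46%.** Section 2.13 does not say that each outcome is tested at each visit. GEE could yield one group-by-time test per outcome. Independence between repeated answers from the same women is also implausible.
- **A regular-and-proficient proportion that does not exist in the data.** Both parts are measured. Only a cut-off and a combining rule are unprinted, and the cited instrument, which cannot be seen here, may define a cut-off.
- **The abstract contradicting section 2.5.1.** The Introduction defines screening uptake as BSE, CBE and mammography, so the abstract's singular is loose wording for that group.

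Nor does the article say that any one significant result will be declared a success. The inflated error follows only if the measures are tested separately at 0.05, each able to support a primary claim.

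**Conclusion.** The point holds in this limited form. The article names three to four primary measures at three follow-ups, with no primary time point or GEE contrast, under one unadjusted 0.05 and a sample size for one unnamed pair of proportions. Separate testing at one time point gives a false-positive chance of 14.3% (three measures) to 18.5% (four) if independent, and about 13% to 17% for four at assumed correlations of 0.7 to 0.3. Testing at all visits, which the text leaves open, would raise this to about 24% to 39% under the assumed correlations, with 46% as the extreme under independence. The regular-and-proficient proportion cannot be derived from the printed rules alone.

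**What to change.** 1. State which outcome 0.71 and 0.43 describe. Name that outcome, at one time point and with one GEE group contrast, as the single primary, and make the other measures and visits secondary. Regular BSE by the existing monthly rule at six months is a candidate, because its rule is printed and six months is the last assessment; it is not the only acceptable choice. If the two proportions describe something other than the chosen primary, the sample size must be redone.
2. If several outcomes must stay primary, apply Holm across them at one named time point.
3. Analyse regular BSE as a proportion and BSEPRI as a separate score, and retitle the outcome accordingly. If a joint proportion is wanted, print the proficiency cut-off and the combining rule.

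**Cost.** No new data are needed. With a single primary, some measures lose primary status. Under Holm with four outcomes, power at the first step (0.0125) is about 60% rather than 79% at 183 participants, assuming the planned difference applies. Recruiting to recover it is not realistic: 269 would be needed, and section 2.9 leaves 289 − 39 = 250 Yemeni teachers in the twelve schools.

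**Timing.** The abstract describes the trial as already conducted, section 2.11 lists the allocated schools, and section 2.14 reports registration. The change is therefore more than wording. It should be a dated amendment made before outcome data are examined; if they have already been examined, the choice should be reported as made afterwards.
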